**PART 2: PROTOCOL INFORMATION**

| **Applicants must complete all sections listed below**  **Sections which do not apply should be completed as ‘*Not Applicable’* and justification provided** |
| --- |
| Study Title (Max. 255 characters) **Risk of adverse mental health outcomes in women with a history of breast cancer in the United Kingdom: a matched population-based cohort study** |
| Lay Summary (Max. 250 words) Women with a history of breast cancer are the largest group of cancer survivors in the general population. A breast cancer diagnosis may impact on mental health, and breast cancer treatments, which are necessary to control the disease, can result in side effects that may negatively affect the women’s quality of life. This study aims to understand whether women who have had breast cancer have different mental health several years post-treatment, compared to women who did not have cancer. For this, we will compare the risk of being diagnosed with anxiety and depression, the primary outcomes of this study, in women who have had breast cancer and in women who never had cancer, attending general practitioner (GP) practices in the UK. We will also compare GP recorded declines in the patients’ memory and thinking capacities, feelings of tiredness and weakness (fatigue), pain, insomnia, sexual problems, or self-harm and suicide (secondary outcomes), between the two groups, and explore factors that may be associated with increased risk of these outcomes. The results of this study can be used to better understand the needs of the women who carry on lives beyond breast cancer. |

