| Objectives, Specific Aims and RationaleGeneral objective To quantify the relative risk of common adverse mental health outcomes in breast cancer survivors compared to women who did not have cancer in the United Kingdom. Specific aims  1. To develop and validate algorithms to identify patients with anxiety and depression (primary outcomes), and fatigue, mild cognitive impairment, pain, sleep disturbance, sexual dysfunction, and fatal and non-fatal self-harm (secondary outcomes) in the CPRD GOLD primary care database. 2. To compare the risk of developing anxiety and depression (primary outcomes), and of recorded fatigue, mild cognitive impairment, pain, sleep disturbance, sexual dysfunction, and fatal and non-fatal self-harm (secondary outcomes), between women with a history of breast cancer and women who did not have cancer. 3. To estimate association between breast cancer history and anxiety/depression by presence of common complications of the breast cancer treatments (i.e. lymphoedema, pain, mild cognitive impairment, fatigue, sexual dysfunction, sleep disorders) and exposure to endocrine therapy.  Rationale It is currently unclear if the long-term mental health of breast cancer survivors differs from that of comparable women who never had cancer. This study will directly address this evidence gap, and help inform prevention and treatment needs relating to the mental health of breast cancer survivors. |

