| Study Background Women with a history of breast cancer are the largest group of cancer survivors in the United Kingdom (UK). Approximately 570,000 women were estimated to be living beyond a breast cancer diagnosis in 2010; this figure was projected to rise to1.5 million women by 2040 [1].  Evidence on the mental health of breast cancer survivors in the UK suggests high levels of distress in this group. Capelan et al [2] reported that 60% of women post treatment for early breast cancer had ≥1 unmet needs; the most common were hot flushes, fatigue, pain, worry, fear or anxiety, and sleep problems. A third of the women who participated in the Standardisation of Radiotherapy Trial (START) [3] had relevant symptoms of anxiety at baseline; five years later, this proportion was 29%. Similar results were observed for depression, albeit the absolute frequency was lower: 12% scored above normal level at baseline, and 11% at the five-year evaluation [3]. The worse recollections reported by a sample of women in the UK seven years after diagnosis included the anxiety related to the future’s uncertainty (38%), the chemotherapy and related side effects (25%), and the shock of the cancer diagnosis (18%) [4]. Other reported concerns were the breast removal and body image implications in sexuality (8%), the suffering induced by their disease in their loved ones (7%), the co-morbidities (6%), and the side effects of radiotherapy and hormone therapy (6%) [4]. All of these may negatively affect the women’s mental status. Indeed, a study on the quality of life of breast cancer survivors one to five years post-diagnosis in England described lower scores than what had been described in other studies of the general population [5].  In the UK, women post-treatment for breast cancer are often followed in hospital outpatient clinics, where they may receive psychological support, and in primary care [6]. In the latter setting, evidence on the relative risk of adverse mental health outcomes in breast cancer survivors, compared to women who did not have cancer, is scant. A systematic review of quantitative studies that evaluated adverse mental health outcomes in breast cancer survivors and in the background female population identified one single study from the UK. In this study, Khan et al [7] used routinely collected primary care data to study the pattern of consultations and prescriptions for anxiety and depression in women with a history of breast cancer for ≥5 years. The results showed significantly increased odds of being prescribed with antidepressants or anxiolytics, even though there was no strong statistical evidence of increased odds of consulting for these conditions. The frequency of anxiety and depression among women diagnosed at <5 years is unknown. Population-based studies conducted elsewhere [8-12] reported highest risks of anxiety and depression shortly after the breast diagnosis, which declined over time. It is currently unclear if this same pattern is observed in the UK. In addition, the studies identified in the systematic review suggest that breast cancer survivors may be at increased risk of other outcomes, such as sleep disturbance, neurocognitive and sexual dysfunctions; no study addressed these in population-based samples of breast cancer survivors in the UK. Furthermore, to our knowledge, the frequency of fatigue, pain, and fatal and non-fatal self-harm, in breast cancer survivors in the UK is unknown, even though these relate to unmet needs often reported by breast cancer survivors. The Clinical Practice Research Datalink primary care database includes data prospectively collected on symptoms, diagnoses, prescriptions, and referrals, for over 5.8 million women being followed in primary care since the late 1980s [13], and therefore it represents a unique opportunity to assess the risk of these outcomes at population-level.  The aim of this study is to quantify the relative risk of adverse mental health outcomes in women with a history of breast cancer the UK, compared to women with no cancer background. The primary outcomes will be anxiety and depression, two common mental disorders that are commonly managed in primary care settings. Secondary outcomes will be fatigue, mild cognitive impairment, pain, sleep disorder, sexual dysfunction, and fatal and non-fatal self-harm; part of the contribution of this study will be to establish the feasibility or otherwise of using electronic health records to assess some of these less-studied outcomes. |

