| Data/ Statistical AnalysisPrimary analysesSpecific aim 1. To develop and validate algorithms to identify patients with anxiety and depression Algorithm development  A systematic review is currently under way to identify the lists of Read codes previously used to define anxiety and depression of primary care databases in the UK. The systematic review search expressions are provided in appendix 5.  *(A) Raw data tabulations*  We will estimate the number and proportion of patients recorded during the observation period with:   1. Diagnostic Read code for anxiety/depression; 2. Prescription of anxiolytics/antidepressants; 3. Referred to mental health services; 4. Symptoms of anxiety/depression.   Proportions will be estimated by calendar year.  *(B) Simpler algorithm*  We will estimate the additional contribution of prescriptions, referrals and symptoms to identify cases of anxiety/depression in CPRD. Referrals and prescriptions of anxiolytics/antidepressants will be considered as sufficient to identify cases of anxiety/depression if a Read code for symptoms of anxiety/depression, respectively, were recorded during the previous year. The reasons for this are threefold: (1) there is good evidence that GPs switched from anxiety/depression diagnostic codes to symptomatic ones [44, 45], following claims of over diagnosis of these conditions; (2) antidepressants and anxiolytics have also other indications, including anxiety disorders for antidepressants [46], which raise questions of the use of these data their own to identify these outcomes; (3) pharmacological treatment of mild depression has been discouraged since 2004 [47], and thus referrals to psychotherapy may help to capture milder cases.  *(C) Complex algorithm*  A more detailed algorithm will be developed considering that some drugs are prescribed for both depression and anxiety, in addition to manage vasomotor symptoms, which may be more frequent in breast cancer survivors than in women who did not have cancer. An example for depression is given in appendix 6. We will estimate the number of patients with anxiety/depression at each step, to evaluate how much each category adds to what has been previously recorded.  Algorithm validation  A random sample of 1 million patients of both sexes will be selected from the CPRD GOLD primary care database. We will apply each algorithm and produce descriptive statistics stratified by likelihood of having the outcome, including:   - Number and proportion of patients with the anxiety, depression or both, by 3-year calendar period; - Number and proportion of patients with the anxiety, depression or both, by 3-year calendar period, age and sex; - Number and proportion of patients with the anxiety and depression by 3-year calendar period and country in the UK.   For each outcome, we will compare the estimates obtained with others obtained from the literature, prioritising national surveys of population-based data such as the following:   - Adult Psychiatric Morbidity Survey 2007 [48] and 2014 [49]; - Measuring National Well-being programme, made available by the Office for National Statistics (includes prevalence of those in the UK with some evidence indicating depression or anxiety, since 2013, by country in the UK and English regions, and by 10-year age groups up to 75 years) [50].   The final algorithm will be chosen by considering information in the numeric value closer to the estimates obtained from the literature. Sensitivity analysis Proportion estimates considering the presence of symptomatic codes within the previous year will be re-calculated to consider shorter periods of time (i.e. 3 and 6 months). Specific aim 2. Risk of mental health outcomes in women who had breast cancer compared to women who did not have cancer**Primary outcomes analysis – depression and anxiety**Main analysis Descriptive statistics including number of events observed and person-years at risk will be computed, overall and stratified by the covariates listed in section M (see above). Medical procedures for the diagnosis of breast cancer are likely to cause anxiety. To deal with this we planned to exclude patients who had a record of anxiety diagnosed within 1 year before the breast cancer; this could result in patients with higher levels of trait anxiety being excluded from the analysis. We will calculate the number and proportion of patients who were excluded because they had the outcome in the year prior to the breast cancer, stratified by month. We will also describe how many of those who were excluded from analysis had an outcome after the breast cancer diagnosis by age-group. The quintiles of the distribution of the number of consultations (defined using the ‘consid’ variable) will be described, as this can indicate the patterns of seeking care between women with a history of cancer, compared to those who did not.  The association between breast cancer history and anxiety and breast cancer history and depression, will be quantified using Cox regression models with time since index as the underlying time scale, and stratifying on matched set to account for matching by age and primary care practice. Follow up will begin at the index date (vide section M for definition of the exposure) and will terminate when an outcome is observed. Women will be censored at the earliest date of any of these: cancer recurrence, other cancer diagnosis, death, transference out of the practice; if these events don’t occur, censoring will be observed at the date of last data collection for the practice. Crude measures of the association between breast cancer history and anxiety and depression will be reported stratifying by the covariates described in section M.  Cox multivariate regression analysis will be use to estimate hazard ratios adjusted for calendar period of breast cancer diagnosis, menopausal status, and diabetes mellitus at baseline (see list of confounders in section L, covariates, for the definition of these variables).  Interaction terms between the exposure and the following variables will be added, to explore effect modification by ethnicity (White, South Asian, Black, Others and mixed), place of residence (care home vs. household), co-habitation status (living alone vs. cohabiting), SES (quintiles of IMD), having mental health disorders history (yes vs. no), having history of stroke (yes vs. no) and coronary heart disease (yes vs. no).  Confidence intervals will be calculated using robust estimates of the standard errors, to account for the fact that patients may also contribute with time at risk in the unexposed cohort prior to their cancer diagnosis.  The proportional hazards assumption will be tested in two ways: 1) graphically, by plotting the cumulative rates on a log scale; 2) inferentially, by applying a likelihood ratio test to the estimates obtained for the entire period of observation and for time split into intervals. Sensitivity analyses Sensitivity analyses planned for this study will include a subset of patients only; this is because they use variables from linked data, which is available for a fraction of the patients only, and include variables amenable to have missing data (i.e. BMI, alcohol intake, smoking and patient-level IMD). Regarding the latter, we will quantify the completeness of each variable to decide on their inclusion in the final models. Analyses including variables with missing data will be restricted to patients with complete data for covariates (complete case analysis), if missing data is likely to be missing not a random. The following sensitivity analyses are planned:   1. The main analysis will be repeated further adjusting for age at diagnosis (continuous variable, since matching allowed for 3-year gap), patient quintile level of IMD, alcohol drinking patterns prior to index date, smoking history and body mass index categories prior to index date. 2. We will exclude women diagnosed with the outcome of interest in the year prior to the cancer diagnosis. To account for the fact that treatment for these conditions may often last for more than one year, and that mild anxiety and depression may be treated in psychological services and not result in visits to the GP, we will repeated the main analysis including only patients who had 5 years of complete follow up prior to the index date and did not have the outcome recorded at any point during this period.  Multiple comparisons We acknowledge that this study includes multiple comparisons for each outcome, and several outcomes. Thus, P-values in the range ~0.01-0.05 be considered as some statistical evidence of an effect and interpreted cautiously. Sample size considerations considering a 0.01 probability of type I error (α) are provided in see section I. Specific aim 3. To estimate association between breast cancer history and anxiety/depression by presence of lymphoedema, pain, mild cognitive impairment, fatigue, sexual dysfunction, sleep disorders, and having done endocrine therapy, during the follow up period. We will estimate the cumulative incidence and period prevalence of lymphoedema, pain, mild cognitive impairment, fatigue, sexual dysfunction, and sleep disorders, in breast cancer survivors during the overall follow up period and by 5-year of follow up period.  We will estimate the hazards of developing anxiety and depression (the main outcomes) for three groups of patients: 1) breast cancer survivors who did not develop the common complication (i.e. lymphoedema, pain, mild cognitive impairment, fatigue, sexual dysfunction, sleep disorders) up to time *t*; 2) breast cancer survivors who have had the common complication at time *t*; 3) women who never had cancer. A Cox regression model will be used to estimate the association between time-updated exposure and the main outcomes (anxiety and depression), having as reference the hazard observed for the women who did not have cancer. The exposure variable will be time-updated; this means that women who develop a common complication will contribute with information to group 1 until the date at which they develop the complication of interest; after this point they will contribute with information to group 2. All models will be adjusted for calendar period of breast cancer diagnosis.  Confidence intervals will be calculated using robust estimates of the standard errors. Sensitivity analyses planned in objective 2 will be applied to this objective as well. Secondary outcomes analyses – fatigue, mild cognitive impairment, pain, sleep disturbance, sexual dysfunction, fatal and non-fatal self-harm The steps outlined above will be repeated for the secondary outcomes. Sensitivity analysis will follow the same rationale as described for the primary analysis. |

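### The main analysis commits to one hazard ratio per outcome averaged from the day of diagnosis, which cannot separate an early excess from a lasting one, although the lay summary and rationale ask about the long term

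*Protocol*

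**What the plan says.** The Lay Summary asks whether women who have had breast cancer "have different mental health several years post-treatment". The Rationale, under Objectives, Specific Aims and Rationale, says "It is currently unclear if the long-term mental health of breast cancer survivors differs from that of comparable women who never had cancer". The Study Background refers to population-based studies in other countries that "reported highest risks of anxiety and depression shortly after the breast diagnosis, which declined over time", and adds: "It is currently unclear if this same pattern is observed in the UK".

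In Data/Statistical Analysis, Specific aim 2, Main analysis, the association with each primary outcome "will be quantified using Cox regression models with time since index as the underlying time scale", stratified on matched set. "Follow up will begin at the index date", and it ends at the first outcome or at censoring. There is no lag or landmark.

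Seven variables are listed for interaction with exposure; time since diagnosis is not among them. The two sensitivity analyses concern extra adjustment and a five-year outcome-free history before the index date. Proportional hazards is checked with a plot and "by applying a likelihood ratio test to the estimates obtained for the entire period of observation and for time split into intervals". The intervals are not named, nothing says that their HRs will be reported, and nothing says what follows if the test rejects. Reporting by five-year period is planned only for the incidence and prevalence of complications in aim 3.

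**The concern.** Two of the protocol's own questions depend on time since diagnosis: whether long-term mental health differs, and whether the early peak seen elsewhere also occurs in the UK. Neither has a planned estimate. The only committed result pools the diagnosis and treatment months with all later survivorship. The same section recognises that diagnostic procedures can provoke anxiety, but deals only with the year before diagnosis.

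A whole-period HR under changing effects is a weighted average whose weights follow the timing of events, and so the distribution of follow-up. A modest effect that lasts and a larger effect confined to the first year can give the same number. With 52,335 exposed women, either can be statistically significant. A reader who wants to know about later years could not tell which applies.

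**Working it through.** The protocol gives no figure for this point, so the check asks what the planned HR would be if the true HR were above 1 in year 1 and exactly 1 afterwards.

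**Inputs from the protocol.** 52,335 exposed women (Feasibility counts); up to four comparators each, so 4 × 52,335 = 209,340; early HRs of 1.25 (anxiety diagnoses) and 1.49 and 1.94 (depression diagnoses) from the literature column of Table 2. Those published values are not year-1 effects; they serve only as a plausible scale.

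**Assumptions.** Constant baseline hazard h0 of 1%, 2% or 4% a year; exponential censoring of 15% a year in exposed and 12% in unexposed women; 15-year maximum; effect confined to year 1.

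**Step 1, the averaged HR.** The Cox estimate b solves Σ[e1(t) − (e1(t)+e0(t))·p(t)] = 0. Here e1 and e0 are expected exposed and unexposed events at t, and p(t) = Y1·exp(b)/(Y1·exp(b)+Y0) with Y1 and Y0 at risk. Expected z is b divided by its model standard error.

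| Early HR | Averaged HR, h0 = 1% / 2% / 4% | Expected z |
|---|---|---|
| 1.25 | 1.040 / 1.041 / 1.045 | 2.0 / 2.8 / 4.1 |
| 1.49 | 1.078 / 1.081 / 1.089 | 3.8 / 5.5 / 8.1 |
| 1.94 | 1.149 / 1.156 / 1.171 | 7.3 / 10.5 / 15.3 |

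At two-sided 0.05, z = 2.0 means power of about 50%, so the weakest case is not reliably significant.

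**Step 2, allowing for matched sets.** Step 1 ignores stratification. With K comparators still at risk in a set whose case is still at risk, the expected score is proportional to h0·K·(HR(t) − exp(b))/(exp(b)+K), averaged over K ~ Binomial(4, q(t)). Here q(t) is the chance that a comparator is still at risk. Solving this gives averages of 1.05-1.06, 1.10-1.12 and 1.19-1.23. Sets lose members over time, so early events weigh more; step 1 is the milder case.

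**Step 3, a hand check.** Take 5% unexposed risk (Table 2), 20% of unexposed events in the early window (assumed) and early HR 1.49.
- Unexposed events: 209,340 × 0.05 = 10,467, of which 2,093 early and 8,374 late.
- Exposed events: 52,335 × 0.05 × 0.20 × 1.49 = 780 early and 52,335 × 0.05 × 0.80 = 2,093 late.
- Early share of all events: (2,093 + 780)/13,340 = 0.215.
- Averaged HR: exp(0.215 × ln 1.49) = 1.09.
- z = 0.0859 × √(0.16 × 13,340) = 3.97, power about 98%.

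Early HRs of 1.25 and 1.94 give 1.05 (power 57%) and 1.16 (near 100%). Letting the early share run from 10% to 50% gives 1.02-1.12 for early HR 1.25 and 1.08-1.43 for 1.94.

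**Step 4, simulation.** With h0 = 1%, mean follow-up of 5 years and a one-year window (20 cohorts per scenario, unstratified), the whole-period HRs were 1.05, 1.09 and 1.18. The HR after the window was 0.99-1.00 each time.

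**Step 5, would the planned test notice?** For early against late, z = ln(HR)/√(sum of 1/events over the four cells). In step 3 this is 0.399/√(1/2,093 + 1/8,374 + 1/780 + 1/2,093) = 8.2. For early HR 1.25 it is 4.4 (power about 99%). With a 10% early share, power is about 91%, falling to about 73% if the unexposed risk is 3%. The test would usually flag the pattern.

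**The case against.** The case on the other side is substantial and limits the point.

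- A reader might infer that an early effect would be published as a long-term risk. The documents do not support that. Nothing says the single HR will be called long-term or kept after proportionality is rejected, and step 5 shows that the planned check would probably detect the pattern.
- A reader might infer that the protocol expects the excess to decline. It reports that pattern from other countries and leaves the UK question open.
- A reader might infer that starting at diagnosis is wrong. It is not. The general objective, aim 2 and the null hypothesis concern women with a history of breast cancer without limit of time, and the background names the first five years as a gap. An overall HR is a legitimate answer to aim 2.
- Cut-points and the handling of non-proportionality are often left to a statistical analysis plan, which is not shown.
- HRs for later bands come from the same first-event model, so they describe women still free of the outcome. They do not remove that selection.

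All of this stands. It does not supply an estimate for the time-dependent questions the protocol itself raises. Detecting non-proportionality is not the same as committing to report the interval HRs, and likely detection makes it more pressing to say what will then be reported.

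The form of the test is secondary. An ordinary likelihood ratio test does not use the robust variance planned because some women contribute to both cohorts, but no material distortion has been shown.

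**Conclusion.** The point holds as a gap between the stated questions and the committed results. The protocol fixes one HR per outcome from the day of diagnosis, promises no HR by time since diagnosis, and attaches no consequence to its proportional-hazards test. With an effect confined to year 1, early HRs of 1.25, 1.49 and 1.94 give whole-period HRs of about 1.04-1.05, 1.08-1.09 and 1.15-1.17, somewhat higher with matched-set stratification. The two larger ones would be clearly significant at this sample size; the smallest only sometimes.

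These sizes rest on assumed baseline hazards, censoring and window length, and on borrowing Table 2's literature values as early effects. That one average cannot tell an early from a lasting excess does not depend on them. The improvement is worth making; it does not invalidate the overall HR as a summary.

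**What to change.** In Specific aim 2, Main analysis, for anxiety and depression:

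- Pre-specify and report HRs by bands of time since diagnosis, for example <1, 1-<2, 2-<5, 5-<10 and ≥10 years, from an exposure × time-band term in the same matched-set-stratified model, alongside the overall HR.
- State that any conclusion about long-term risk will rest on the later bands, and that these apply to women still free of the outcome.
- Preferably test the exposure × time term with a Wald test using the planned robust variance.

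The cost is a few lines of protocol and code, since time-splitting is already planned for the proportional-hazards test. The downside is wider confidence intervals within each band.
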